### Objectives and Hypothesis

The primary objective is to assess the effect of SMS reminders, telephone calls, and transport incentives on completion of TB diagnosis among persons with presumed TB and initiation of treatment for diagnosed patients. The secondary objectives are to determine the median turnaround time for TB diagnosis and treatment initiation and to examine the acceptability and feasibility of the interventions. We hypothesize that compared to standard of care (SOC), each individual intervention—SMS reminders alone or telephone calls alone—will improve completion of TB diagnosis and initiation of treatment by reducing prediagnosis LTFU by a minimum of 40% (from 24% to 14.4%), while a combined intervention—SMS reminders or telephone calls coupled with transport incentives—will reduce prediagnosis LTFU by 50% (from 24% to 12%). This protocol follows the SPIRIT (Standard Protocol Items: Recommendations for Interventional Trials) reporting guidelines [27].

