### Trial Design, Population, and Eligibility

This will be a multicenter individual randomized controlled trial with five arms: (1) SOC (control arm), (2) SMS reminders only, (3) telephone calls only, (4) SMS reminders and a transport incentive, and (5) telephone calls and a transport incentive. This intervention was designed and adapted through stakeholder engagements in a co-design workshop. The original design included SMS reminders only and a transport incentive [34]. However, based on stakeholder engagements, telephone calls were added to address the following concerns: (1) the risk of unintentional disclosure if someone other than the recipient reads the SMS text message; (2) existing SMS fatigue due to high volume of messages from telecom companies, leading to a likelihood of messages being ignored or deleted; (3) lack of real-time 2-way communication; and (4) lack of usefulness for patients who cannot read. Telephone calls were preferred because they offer privacy and foster 2-way communication in real time .

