### Sample Size Estimation

An estimated sample size of 2389 participants was determined to achieve 80% power at a type I error of 5%, adjusted for multiple comparisons using the Bonferroni correction. Four comparisons were considered according to the study objectives; therefore, the adjusted level of significance is 1.25%, with a corresponding 2-tailed Z value of 2.238. We also adjusted for a 24% LTFU among patients with TB, based on findings from the formative study that informed the design of these interventions. We assumed a 40% reduction in LTFU based on previous similar studies [36,37] for comparisons between SOC and either SMS reminders alone or telephone calls alone, resulting in an assumed proportion of LTFU of 14.4% in both these groups. For comparisons between SOC and combined interventions (SMS reminders or telephone calls with a transport incentive), a 50% reduction will be considered clinically significant, given the expected higher impact of the incentive. The sample size has been further adjusted for clustering using a design effect of 1.5 to account for the clustering anticipated at the health facility level and a postenrollment attrition rate of 20%.

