### Randomization and Blinding

Eligible participants will be randomly assigned by research assistants to 1 of the 5 study arms using permuted block randomization in a ratio of 2:2:2:1:1 via a predesigned mobile app (Figure 2). The block sizes will be varied to minimize predictability. A computer algorithm will be designed by the biostatistician together with the app designer to generate the allocation sequence in blocks of 8 and 16, assigning their order randomly. The allocation sequence will then be input into the predesigned mobile app for automatic randomization once the research assistants input the participant’s unique study ID number. Due to the nature of the interventions, participants will not be blinded to their assigned study arm. Research assistants will also not be blinded, given their role in delivering the interventions. However, the outcome assessors and data analyst will remain blinded to the study arms.

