### Data Management and Analysis

#### Overview

ODK data will be downloaded into Microsoft Excel and transferred to Stata 14 (StataCorp LLC) for cleaning and analysis. The primary analytical approach will follow the intention-to-treat principle, with participants in the intervention arm considered exposed to the intervention regardless of whether they received specific intervention services. We will assess for any contamination by conducting and comparing the results of the intention-to-treat and per-protocol analyses. Descriptive statistics (means, medians, and proportions) will be used to describe participant characteristics across the study arms. We will control for characteristics that are not balanced across the study arms in the fitted regression models. Chi-square tests will be performed for categorical outcomes. Log-binomial regression models using generalized linear modeling will be applied to assess associations between each intervention and the outcomes. A *P* value <.05 will be considered statistically significant.

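### The design effect of 1.5 for facility clustering does not follow from individual randomisation, so the stated 80% is not the power of 2389 participants; on the plan's inputs it is about 90% or more

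*Protocol article*

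**What the plan says.** The Sample Size Estimation section gives the target and its basis: "An estimated sample size of 2389 participants was determined to achieve 80% power at a type I error of 5"%, with a Bonferroni correction for four comparisons. It then states that "the adjusted level of significance is 1.25%, with a corresponding 2-tailed Z value of 2.238". The control rate of loss before diagnosis is 24%. A 40% reduction is assumed for SMS alone or calls alone, "resulting in an assumed proportion of LTFU of 14.4% in both these groups", and a 50% reduction (to 12%) for the two arms that add the transport incentive. Two inflations follow. One is for 20% attrition. The other is the subject of this point: "The sample size has been further adjusted for clustering using a design effect of 1.5 to account for the clustering anticipated at the health facility".

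The design is described elsewhere in the article. Under Trial Design, Population, and Eligibility: "This will be a multicenter individual randomized controlled trial with five arms". Under Randomization and Blinding: "Eligible participants will be randomly assigned by research assistants to 1 of the 5 study arms using permuted block randomization", in the ratio 2:2:2:1:1 and in blocks of 8 and 16. There are six facilities (Study Setting). For the analysis, the Overview under Data Management and Analysis states "Chi-square tests will be performed for categorical outcomes" and names log-binomial regression; the Abstract names modified Poisson regression.

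**The concern.** A clustering design effect describes the loss of information when whole facilities are allocated to arms, because differences between facilities then become differences between arms. Here the arms are formed within facilities. A facility with high loss to follow-up raises the rate in all of its arms alike, and that shared level drops out of the contrast. The spread between facilities is already contained in the binomial variance p(1 − p), so multiplying by a further 1.5 allows for variance that the comparison does not carry.

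The 80% is therefore the power of a comparison that the trial does not make. With recruitment nearly complete (2355 by 28 August 2025, per Results), the main remaining uses of this statement are reading non-significant comparisons and deciding whether to extend recruitment. It also interacts with a separate error in the same section, the Z value. Someone who repairs only that one is led to the wrong conclusion about the size of the trial.

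**Working it through.** **Inputs.** From Sample Size Estimation and Objectives and Hypothesis: p0 = 0.24 (control), 0.144 (single-intervention arms), 0.12 (combined arms), Z = 2.238, power 80% (z = 0.8416), design effect 1.5, attrition 20%. From Randomization and Blinding: 2:2:2:1:1, so control and each single-intervention arm take 2/8 of the total and each combined arm 1/8.

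**1. Reproducing 2389.** Pooled two-proportion formula, 24% v 14.4%, mean rate 0.192:

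n = [2.238 × √(2 × 0.192 × 0.808) + 0.8416 × √(0.24 × 0.76 + 0.144 × 0.856)]² / 0.096² = (1.2466 + 0.4653)² / 0.009216 = 318.0 per arm.

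Total = 318.0 × 4 × 1.5 / 0.8 = 2385, against 2389 stated. Using 2.241 for Z gives 2390. Without the 1.5 the total is 318.0 × 4 / 0.8 = 1590, so about 795 participants come from the design effect.

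**2. The Z value.** 2.238 leaves 1.26% in one tail and 2.52% in two. The two-sided value for 1.25% is 2.498. This is a separate error, but it changes the restated power, so both values are carried below.

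**3. Power of 2389 after attrition.** Control and single-intervention arms: 2389 × 0.8 / 4 = 477.8 each. Combined arms: 238.9 each. To apply a design effect, divide these by 1.5.

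Example, 24% v 14.4%, no design effect, Z 2.238: pooled SE = √(0.310272 / 477.8) = 0.02548; unpooled SE = √(0.305664 / 477.8) = 0.02529; (0.096 − 2.238 × 0.02548) / 0.02529 = 1.54, which is 93.8% power.

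| Z | Design effect | Single v control | Combined v control |
|---|---|---|---|
| 2.238 | 1.5 | 80.1% | 82.7% |
| 2.238 | 1 | 93.8% | 95.6% |
| 2.498 | 1.5 | 72.0% | 74.4% |
| 2.498 | 1 | 90.0% | 92.3% |

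The first row is the stated 80%. At Z 2.498, n is 374.0 per arm, so 80% power needs 374.0 × 4 / 0.8 = 1870 participants without the factor and 2805 with it.

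**4. Is the factor about 1?** Simulations used individual allocation over six facilities, 478 per arm, and the unadjusted two-proportion test at Z 2.498 (24% v 14.4%). Facility rates and ICCs are assumptions.
- Facility control rates fixed between 8% and 40% (mean 24%, ICC about 0.07), with the same 40% relative reduction everywhere: false-positive rate 1.25% without stratification and 1.0% with arms balanced by facility; power 90.2% and 90.7%.
- Facility rates drawn at random and shared across arms: false-positive rate stayed close to 1.25%. In one set of runs power was 89.8% at ICC 0 and 88.8% at ICC 0.05. In another it was 88.1% at ICC 0.05 and 86.2% at ICC 0.10.

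All of these lie well above the 72% that a true factor of 1.5 would produce.

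**The case against.** The strongest reply is that the factor may be doing real work. The facilities range from a national referral hospital to a health centre IV. The article describes cartridge shortages, missing on-site equipment and thin laboratory staffing, which affect when results are ready and hence when the second reminder goes out. Control care includes irregular messages and calls. The effect could well differ by facility, and then the variance does inflate for inference beyond these six sites. The arithmetic supports this: with six equal facilities, a between-facility SD of 4.4 percentage points around the 9.6-point effect adds 0.044² / 6 = 0.000323 to a sampling variance of 0.305664 / 477.8 = 0.000640, an inflation of 1.5. Simulated at that SD (an assumption), power was about 85% and the false-positive rate for a zero average effect was 3.7% to 3.8%. This stands as a limit: a factor near 1 is conditional on effects not varying materially between facilities. It does not rescue the text, which gives clustering as the reason and assumes no such variation.

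It can also be said that a number giving 90% or more does achieve 80%, that recruitment is almost done, and that an article's short list of tests may not be the whole analysis. The error is indeed on the safe side and costs no participant anything. The figure is still wrong for this design. The last remark limits the restated power to an analysis that does not bring in a clustered variance.

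Finally, simply striking out the 1.5 would leave 2389 without a derivation, since the remaining inputs give about 1590. That objection is right and shapes the remedy.

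**Conclusion.** The point holds in a conditional form. Under individual randomisation with facilities contributing to all arms, facility levels shared by the arms do not inflate the between-arm variance, so a 1.5 described as a clustering adjustment is not justified by the stated design. The understatement of power is 14 percentage points for the single-intervention comparisons at the printed Z (94% against the stated 80%), or 10 points at a true two-sided 1.25%. These figures rest on the plan's event rates, 20% attrition, no material variation of effect between facilities, and an analysis without a clustered variance.

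Three stronger readings are not supported:
- That the trial is underpowered or should recruit to about 2805. This arises only if Z is corrected while the 1.5 is treated as real.
- That facility differences can never matter here. That would require the absence of effect variation, which the article does not establish.
- That the 1.5 is too small because a cluster formula would give far more, for example about 17 with an ICC of 0.05 and some 319 analysed per facility. The article gives no such ICC, and the formula is for a design that this trial does not have.

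**What to change.** In Sample Size Estimation:
- Keep the statement that 2389 was obtained with a factor of 1.5, so that the number remains traceable.
- Stop presenting the factor as a required adjustment for clustering. Call it a conservative allowance and, if that was the intention, say that it covers variation of the intervention effect between facilities.
- Correct the critical value to 2.498 in the same edit.
- State that, without the allowance and after 20% attrition, 2389 participants give about 90% power for each single-intervention comparison and about 92% for each combined comparison at a two-sided 1.25%.

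The cost is a sentence or two and one restated power figure. Recruitment, allocation and conduct are untouched. The only thing given up is a nominal margin if effects prove to vary between facilities, and the relabelled allowance makes that margin explicit.

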### Study Population

The study population will comprise persons with presumed TB who did not complete diagnosis on the same day as their health facility visit. Persons with presumed TB will be defined as those presenting with signs and symptoms suggestive of TB, including cough, fever, night sweats, and unexplained weight loss.

We will include (1) patients referred for Xpert MTB/RIF testing; (2) those aged 18 years or older; (3) those currently residing in the health facility’s catchment area; (4) those willing to consent to the study procedures, including follow-ups, and able to sign an informed consent form; (5) those who own a mobile phone and have it in their possession on the day of recruitment; and (6) those able to read (a test SMS text message will be sent to the patient’s mobile phone, and they will be asked to read it aloud). Participants planning to move out of the study area within 3 months after enrollment and those participating in other related studies (eg, those involving SMS reminders, telephone calls, or transport incentives) will be excluded.

### Randomization and Blinding

Eligible participants will be randomly assigned by research assistants to 1 of the 5 study arms using permuted block randomization in a ratio of 2:2:2:1:1 via a predesigned mobile app (Figure 2). The block sizes will be varied to minimize predictability. A computer algorithm will be designed by the biostatistician together with the app designer to generate the allocation sequence in blocks of 8 and 16, assigning their order randomly. The allocation sequence will then be input into the predesigned mobile app for automatic randomization once the research assistants input the participant’s unique study ID number. Due to the nature of the interventions, participants will not be blinded to their assigned study arm. Research assistants will also not be blinded, given their role in delivering the interventions. However, the outcome assessors and data analyst will remain blinded to the study arms.

**Figure 2. F2:**
[figure not shown]
Flow diagram for randomization. SOC: standard of care; TB: tuberculosis.

### Recruitment Strategies for Study Participants

Two research assistants will be strategically positioned at different potential entry points for persons with presumed TB in each study health facility. The entry points will include the outpatient department, antiretroviral therapy (ART) clinic, prenatal clinic, and TB unit. The inpatient units will be excluded because admitted patients are less likely to be lost to follow-up, as they remain within the health facility throughout the testing process. In each study facility, we will hold entry meetings with health workers from the various departments involved in identifying persons with presumed TB to inform them about the study and solicit their support in referring eligible patients throughout the study period.

Referred patients will be introduced to the study team and asked whether they are interested in participating. Those who express interest will be given a card and requested to return to the study desk once they complete care seeking. The card will serve as a reminder not to leave the health facility before returning to the study desk. Patients who return after completing care seeking will be assessed for eligibility, and those who meet the criteria will be asked to provide informed consent by signing the consent form. Eligible participants will then be enrolled and randomly assigned to 1 of the 5 study arms using a smartphone preloaded with the randomization app. All participant details will be recorded in the study registers for persons with presumed TB in both electronic and hard-copy formats for backup.

### Participant Follow-Up Procedures

Follow-up interviews will be conducted after 30 days from the day of recruitment for all participants primarily through face to face interviews at the health facility. Home visits will be conducted for patients who fail to turn up at the health facility. If still we can not access the patient, telephone calls will be made by research assistants to conduct the interview over the phone. At follow-up, data will be collected on whether the TB tests had been performed, along with the date of the TB test results, the date of registration for TB treatment, and the TB registration number. If a participant does not submit a sputum sample, receive test results, or initiate treatment after diagnosis, they will be asked to provide reasons for not undergoing testing, receiving results, or starting treatment.

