#### SMS Reminders Only

Participants in this arm will receive up to 3 SMS reminders. The first reminder will be sent on day 0, the day of study enrollment. The second reminder will be sent once the patient’s results are ready. If the patient does not return to complete the TB diagnostic process (ie, testing and receiving results) within 1 day of the second reminder, a third reminder will be sent. This third reminder will serve as a reinforcement, reminding participants to return and complete diagnosis or initiate treatment if they have not already done so. Standardized SMS reminders will be manually sent by the research team through the telecom service providers MTN and Airtel in either Luganda (the local language) or English, based on the participant’s language preference determined at enrollment. The SMS reminders are planned to be 1-way (unidirectional) and the content neutral, excluding any mention of the word “TB” or the patient’s name. The specific wording of the SMS reminders will be co-designed with stakeholders including persons with presumed TB and health workers. Quality control officers will verify the SMS reminders sent daily, checking for the correctness of recipient telephone numbers and ensuring that all reminders are sent on time as per the study procedures. Each day, quality control officers will randomly select at least 4 participants from the SMS reminder arm or from among those scheduled to receive the second or third reminder and cross-check their details on the study telephone to confirm that the participant received the appropriate SMS reminder and in the preferred language. They will also cross-check the correctness of the telephone number that received the SMS reminder vis-à-vis the one recorded in the register for persons with presumed TB. Successful transmission of reminders will be checked by requesting sample statements from the telecom companies to confirm SMS dispatch to patients. Moreover, at follow-up, participants will be asked whether they received either an SMS reminder or a telephone call and a transport incentive, further corroborating whether the participant received the SMS reminder.

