### Data Collection Procedures

Participants will be enrolled in the study and assigned a unique ID number, which will be used for randomization using the mobile app. Once the participant has been randomly assigned, baseline measurements and tracking information will be collected and recorded using the Open Data Kit (ODK) platform (Get ODK Inc) and directly uploaded to the server. Data will be collected on age, sex, occupation, date when identified as a person with presumed TB, distance to the health facility of enrollment, test method used (ie, sputum smear microscopy or Xpert MTB/RIF), and knowledge and perceptions about the disease and treatment. We will train outcome assessors to objectively conduct interviews and assess outcomes at follow-up. This approach will minimize any biases associated with the team administering the intervention.

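### Fallback telephone follow-up is given to research assistants, whom the protocol calls unblinded, so the stated blinding of outcome assessment does not hold for participants interviewed that way

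*Protocol article*

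**What the plan says.** Randomization and Blinding separates two roles. On the delivery side: "Research assistants will also not be blinded, given their role in delivering the interventions". The same section has this role carry out allocation: "Eligible participants will be randomly assigned by research assistants to 1 of the 5 study arms". On the assessment side: "However, the outcome assessors and data analyst will remain blinded to the study arms".

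Data Collection Procedures presents the separate assessors as a safeguard: "We will train outcome assessors to objectively conduct interviews and assess outcomes at follow-up", followed by "This approach will minimize any biases associated with the team administering the intervention".

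Participant Follow-Up Procedures sets out three steps at day 30: an interview at the facility, a home visit for those who do not come, and, if that also fails, "telephone calls will be made by research assistants to conduct the interview over the phone".

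The SMS Reminders Only section adds a delivery check: "at follow-up, participants will be asked whether they received either an SMS reminder or a telephone call and a transport incentive". Table 1 lists receipt of interventions in the day-30 column, alongside sputum submission and receipt of results.

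**The concern.** The primary endpoint needs two events within 30 days: a sputum sample submitted and the result received by the patient. The only collection route the article describes is the follow-up interview, and participants know their arm. Blinding the person who records the answers is therefore a safeguard that matters.

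The telephone step comes last, after two failed attempts, so it may well hold a higher share of non-completers than the other modes. These are the participants whose coding determines the arm difference. At this step the text hands the interview to the role that allocated the participant and, in the call arms, made the reminder calls. An interviewer who knows the arm may probe or code doubtful answers differently by arm.

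**Working it through.** The point rests on comparing sections. The plan gives no figure on it to reproduce.

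**Step 1. Who does what.**

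| Task | Role named | Section | Blinded? |
|---|---|---|---|
| Allocation through the app | Research assistants | Randomization and Blinding | No |
| Repeated attempts at intervention calls | Research assistants | Telephone Calls Only | No |
| Follow-up interviews and outcome assessment | Outcome assessors | Data Collection Procedures | Stated as yes |
| Fallback telephone interview | Research assistants | Participant Follow-Up Procedures | No, by the role's own description |

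The last two rows conflict. The article mentions no second, blinded group of research assistants. If one exists, the text does not say so.

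**Step 2. Reach of the conflict.** It covers only participants missed at the facility and at home and then reached by telephone. The role is not named for facility interviews and home visits in that section, and Data Collection Procedures assigns follow-up interviews to outcome assessors.

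**Step 3. The receipt question.** The sentence stands in the SMS section, but its wording covers SMS, call and incentive, and Table 1 is not arm-specific. The answer can disclose the arm. Whether this affects the outcome coding depends on question order, which is not given. It is a risk, not a demonstrated breach.

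**Step 4. Scale.** Let p be true non-completion, f the share of non-completers interviewed by telephone, and m the share of those wrongly recorded as completers. With no true effect, the spurious difference between an intervention arm (I) and standard of care (S) is

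p × (f_I × m_I − f_S × m_S).

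Only p = 0.24 is in the documents (Objectives and Hypothesis). Values of f and m below are assumptions, and the SOC term is set to zero, which is the extreme one-sided case.

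| f_I | m_I | Spurious gain | Share of the 9.6-point target (24% − 14.4%) |
|---|---|---|---|
| 0.25 | 0.05 | 0.24 × 0.0125 = 0.3 points | 3% |
| 0.25 | 0.10 | 0.24 × 0.025 = 0.6 points | 6% |
| 0.25 | 0.20 | 0.24 × 0.05 = 1.2 points | 12.5% |
| 1.00 | 0.20 | 0.24 × 0.20 = 4.8 points | 50% |

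The last row needs every non-completer to be interviewed by telephone, so it is a ceiling for that error rate.

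For the effect on false positives, a full-size arm has 2389 × 2/8 = 597 participants, or 597 × 0.8/1.5 = 318 effective after the stated attrition and design effect. At a two-sided 1.25% level (critical value 2.498), the chance of a false result favouring a single-intervention arm is 0.6% with no error. It is about 1.6% at a 1.2-point spurious gain and about 15% at 4.8 points. The range is wide because f and m are unknown.

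**The case against.** Several counter-arguments have force.

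- **Other data sources.** The article does not say self-report is the only source. Follow-up collects the date of test results, the date of treatment registration and a TB registration number, and Study Setting describes laboratory and unit TB registers. A reader might infer that the primary endpoint is largely self-reported. The documents do not establish that, and a condensed article commonly leaves source verification to the full protocol. This stands.
- **Other protections.** A reader might infer that assessor blinding is the plan's only protection. It is not: assessors are trained, the analyst is blinded, and Study Strengths and Limitations acknowledges that blinding is incomplete, naming participants in particular. That passage does not, however, withdraw the claim about assessors.
- **Size of the telephone group.** A reader might take the 20% attrition allowance as evidence that this group is large. It is not evidence of that. Attrition allows for participants lost after enrolment, whereas fallback interviewees are those who were reached.
- **Question order.** If outcome items come first, the receipt question cannot influence them. Silence on form order is not an error.
- **Arm-related success of the calls.** That call-arm participants would answer more readily is plausible but not documented.

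None of this resolves the conflict over who conducts the telephone interviews.

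**Conclusion.** The contradiction is in the current text. The assessor blinding claimed for the primary endpoint does not hold for participants interviewed by telephone, unless those callers are in fact blinded staff whom the article does not describe. The receipt question at the same visit adds a risk that depends on an unstated order.

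The bias cannot be sized. A reader might be drawn to figures of 12.5% to 50% of the target effect. These assume 5% to 20% error among all non-completers and none in standard of care, whereas the conflict reaches only the telephone subgroup. The documents support neither assumption, so the figures show scale only. The conclusion is that a stated safeguard fails for a subgroup of unknown size, not that the trial result is biased by a known amount. It should be put right before results are reported.

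**What to change.** **Remaining follow-up.** Have the existing blinded outcome assessors make the fallback calls. In the ODK form, record and lock the outcome items before the intervention-receipt items. Because 2355 of 2389 participants had been recruited by 28 August 2025 (2389 − 2355 = 34 to go), this can help only the last participants.

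**Participants already followed.**

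1. Reconcile the sections by stating who made the telephone interviews, and correct the blinding statement if research assistants did.
2. Tabulate interview mode (facility, home, telephone) and interviewer role by arm.
3. Add a sensitivity analysis of the primary outcome by interview mode or interviewer role.
4. Check sputum submission and result dates against laboratory registers, where these record them, by someone who does not see the arm.

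**Cost.** Some reassignment of tasks and a modest abstraction exercise. The main limit is that no section says a register records the patient's receipt of the result. The register check can verify testing but may not verify the full endpoint, so recoding the primary outcome from registers alone is not recommended. Nor can it be assumed that registers under-record equally across arms.
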